#### Secondary Outcomes

(a) Serial head circumference as an index of brain weight

(b) Longitudinal thyroid hormone concentrations between birth and expected date of delivery;

(c) Cortisol hormone status between birth and expected date of delivery

(d) Auxological data at pre-randomisation, day 14, day 21, day 28 and at 36 weeks' CGA

(e) Thyroid gland size measured by ultrasound imaging

(f) Mortality

(g) The volumes of key brain structures, whole brain volume, extent of myelination of cerebral white matter and white matter integrity and brain vessel morphology using brain MRI examinations at term equivalent

(h) Duration of mechanical ventilation/oxygen requirement

(i) Chronic lung disease requiring home oxygen at discharge

## Methods

### Trial Design

A multicentre double blind randomised placebo controlled trial of levothyroxine given postnatally to infants born under 28 weeks' gestation until 32 weeks' CGA. Parents, care providers and outcome assessors will be blind to the allocation of placebo and levothyroxine.

### Inclusion Criteria

a) Infants with gestational age under 28 weeks at birth*

b) Recruitment within five days of birth

c) Single or multiple births

*The assessment of gestational age will be based on the working estimate available in the obstetric notes at the time of delivery (corrected gestational age).

### Exclusion Criteria

a) Infants born to mother with known thyroid disease or on antithyroid medications during pregnancy will be excluded.

b) Infants born to mother who are on amiodarone during pregnancy will be excluded.

c) Infants diagnosed with major congenital or chromosomal abnormalities known to affect thyroid function or brain development will be excluded.

d) Maternal death during or within 5 days after childbirth.

### Randomisation

Once all inclusion and exclusion criteria are met and informed consent has been obtained, infants will be included in the study and allocated a randomisation number. The randomisation lists will be computer generated with random variable block lengths using the statistical package STATA. The randomisation list will be stratified by centre, and gestational age at birth (under 25 weeks' gestation, 25–26 weeks' gestation, 27–27^+6 ^weeks' gestation). Multiple births will follow the randomisation process as per singleton births: each sibling in a multiple birth will receive the same treatment allocation.

Concealment of allocation will be provided by pharmacy departments of the respective hospitals. The randomisation list will be stored in a locked filing cabinet in the pharmacy Departments of each hospital and access will be limited to the pharmacist involved in the study.

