## Statistical Consideration

### Sample Size Calculation

A sample size of 64 in each group will have 80% power to detect a difference between the means of the thyroxine and placebo groups of 0.67 mm (0.5*SD) for the outcome subarachnoid space at 36 weeks' CGA. This assumes that the common standard deviation is 1.3 mm and analysis is based on using a two group t-test with a 0.05 two-sided significance level. The value for the SD is taken from Armstrong et al[54] who report subarachnoid space as an indirect method of brain growth in preterm infants.

To ensure the appropriateness of the SD used in our calculations we will run an internal pilot after the first 30 infants have been randomised. We will compare the SD of these 30 infants with the standard deviation of Armstrong et al[54]. An internal pilot[49] can be used to increase but not decrease the size of the study. Assuming the 20% loss to follow up that we have experienced in an ongoing trial on the unit, we aim to recruit and randomise 150 infants with gestation below 28 weeks'.

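### Siblings share one allocation, but the sample size treats every infant as independent, so the stated 80% power is optimistic

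*Protocol article*

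**What the plan says.** The Inclusion Criteria admit "Single or multiple births", with no limit of one infant per family. The Randomisation section adds that "each sibling in a multiple birth will receive the same treatment allocation" and stratifies the list by centre and by three bands of gestational age.

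The Sample Size Calculation states: "A sample size of 64 in each group will have 80% power" to detect 0.67 mm, labelled as half an SD, in subarachnoid space at 36 weeks. It assumes "the common standard deviation is 1.3 mm" and that "analysis is based on using a two group t-test with a 0.05 two-sided significance level". The target allows only for attrition: "Assuming the 20% loss to follow up", "we aim to recruit and randomise 150 infants". The internal pilot re-examines one input, the SD: "We will compare the SD of these 30 infants with the standard deviation of" the published source. The share of multiples, a sibling correlation and a design effect do not appear.

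The Analysis section assigns mixed models to longitudinal data and log-rank and Cox methods to survival outcomes. It names no test for the single 36-week measurement and refers to a separate statistical analysis plan, which is not shown.

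**The concern.** Siblings share a mother, a gestation and antenatal exposures, so their subarachnoid widths are likely to be positively correlated. When they also share an arm, that correlation enters the variance of the difference between arms: two siblings carry less information than two unrelated infants. A calculation that counts infants as independent then overstates power.

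A t-test on infants would also compute its standard error as if allocation had been by infant. The primary p-value and confidence interval would then not reflect how infants were allocated. The internal pilot would not reveal the problem, because sibling correlation does not show in the overall SD.

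**Working it through.** **Inputs from the protocol:** 64 per group; SD 1.3 mm; difference 0.67 mm, labelled 0.5 SD (0.5 × 1.3 = 0.65 mm); two-sided 5% t-test; 150 randomised; 20% loss.

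**Assumed, because the protocol does not give them:** f, the share of infants who are analysed members of a twin pair, 0.20 to 0.35; ρ, the sibling correlation, 0.3 to 0.7. All multiples are taken as twins.

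**Step 1: reproduce the plan's figure.** At 0.5 SD, a two-sample t-test with independent infants needs 63.8, so 64 per group, with power 80.1%. The stated size therefore contains no design effect. With the literal 0.67/1.3 = 0.515 SD, 64 per group has 82.5% power.

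**Step 2: design effect.** For an unweighted difference in means with twins in the same arm, DE = 1 + f × ρ.

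- Low: 1 + 0.20 × 0.3 = 1.06
- Middle: 1 + 0.25 × 0.5 = 1.125
- High: 1 + 0.35 × 0.7 = 1.245

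**Step 3: power at effective size n/DE, if strata explain no outcome variance.**

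| Case | 64 per group, 0.5 SD | 64 per group, 0.67/1.3 | 60 per group, 0.5 SD | 60 per group, 0.67/1.3 |
|---|---|---|---|---|
| No clustering | 80.1% | 82.5% | 77.5% | 80.0% |
| Low | 77.8% | 80.2% | 75.1% | 77.6% |
| Middle | 75.3% | 77.8% | 72.5% | 75.1% |
| High | 70.9% | 73.5% | 68.1% | 70.7% |

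The 60 per group is what the target leaves at the stated loss: 150 × 0.8 = 120. That shortfall against 128 is a separate matter. It is shown only because it removes the slack that the literal 0.67 mm reading would otherwise give.

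A mixed model that weights families efficiently has variance inflation 1/[(1 − f) + f/(1 + ρ)]. In the middle case this is 1/(0.75 + 0.25/1.5) = 1.091, and power at 64 per group and 0.5 SD is 76.6% instead of 75.3%.

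**Step 4: type I error of an unadjusted t-test, if it were used.** With no variance explained by the strata, the error is 2 × [1 − Φ(1.96/√DE)]: 5.7% (low), 6.5% (middle), 7.9% (high).

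**Step 5: effect of stratification.** Siblings share centre and gestation band, and allocation is balanced within these. Let v be the share of outcome variance that the strata explain. The part of the sibling correlation due to strata then does not inflate the arm difference, while the unadjusted t-test still counts v as noise. The ratio of true to assumed variance is

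(1 − v) + f(ρ − v) = 1 + fρ − v(1 + f).

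The error exceeds 5% only if fρ > v(1 + f). The break-even v is 0.06/1.20 = 0.05 (low), 0.125/1.25 = 0.10 (middle) and 0.245/1.35 = 0.18 (high). A simulation of the middle case (128 infants, 3 or 9 strata, blocks of 4 or 6, 6,000 runs each) agrees: 6.1% to 6.5% at v = 0, 4.7% to 5.6% at v = 0.10, and 4.0% to 4.7% at v = 0.20. The protocol gives no value for v.

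**The case against.** The strongest reply is that the t-test is stated only as the basis of the sample size. The Analysis section fixes no test for the primary outcome, and the unseen analysis plan may well include a family term. This stands. A reader might infer that the primary analysis will understate its standard errors and exceed 5% type I error, but the protocol does not establish that. Even if the t-test were used, Step 5 shows that stratification could bring its error to 5% or below.

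A reader might also infer that 80% power is certainly missed at 64 per group. That too is not supported across the whole range: on the literal 0.67 mm and 1.3 mm, the low case keeps 80.2%. The power figures also assume v = 0. Stratum variance reduces the net clustering, and loss to follow-up breaks some pairs, which lowers f. The design effects are therefore upper values for each assumed pair of f and ρ.

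What the reply does not remove is the sample size itself, which is fixed in this document and makes no allowance for shared allocation. A family-level model in the analysis plan would correct the standard errors, but it would not restore information lost to sibling correlation.

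**Conclusion.** The concern holds in a limited form. The Randomisation section allocates families, the Sample Size Calculation counts independent infants, and the two have not been reconciled, so the stated 80% is optimistic. With 20% to 35% of infants being twins and a sibling correlation of 0.3 to 0.7, power at 64 per group is about 71% to 78% at 0.5 SD or 73% to 80% at 0.67/1.3. At the 60 per group that 150 randomised and 20% loss would leave, any net clustering takes power below 80% on either reading of the effect size.

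The type I error point is conditional twice: on the t-test being used for the primary analysis, and on the strata explaining little of the outcome. Its upper values are 5.7% to 7.9%. The sizes rest on assumed values of f and ρ, which the protocol does not give. Severity is moderate: the middle case costs about five points of power in an explanatory trial, and the remedy is simple.

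**What to change.** State that the primary and other infant-level outcomes will be analysed with mother as the cluster, by a random intercept for mother or by GEE or cluster-robust standard errors, adjusting for centre and gestational-age band. If the analysis plan already says this, a cross-reference in the protocol is enough.

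Restate power with a declared share of multiples and sibling correlation, using 1 + f × ρ or the mixed-model equivalent, and show a range. Allocation and enrolment stay as they are. The cost is a sentence in the Analysis section, a revised power statement, and a slightly lower stated power.

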#### Blinding and Unblinding

Parents, investigators, clinicians involved in patient care and individuals assessing and analysing study end-points will all be blinded to the allocated study treatments. Levothyroxine and its placebo will be presented identically (see below). In the event that unblinding is necessary, there will be 24 hour access for unblinding and an Unblinding Case Report Form will be completed. In most cases, stopping the 'treatment' should be sufficient without the need for unblinding. Before unblinding is done, the case will be discussed with the Chief Investigator or in his absence a delegated member of the Trial Management Group.

### Treatment Regimen and Dosage

We will use two forms of the active medication: intravenous levothyroxine (tradename: Levothyroid) and oral levothyroxine solution (tradename: Evotrox) with corresponding placebos during the study period.

In the initial phase, infants will receive either intravenous Levothyroid or placebo (5% dextrose) within the first 5 days after birth. The treatment regimen will follow the dosage guidelines determined by previous studies[8,52] at 8 mcg/kg birthweight/day single daily dose.

In the next phase, once enteral feeds are fully established, oral solution Evotrox or placebo (carrier solution without active drug) will be given at 8 mcg/kg birthweight/day single daily dose until the baby reaches 32 weeks CGA.

### Study Medication

The intravenous levothyroxine (Levothyroid) medication is a powder and is dissolved in 5% dextrose and albumin and aliquots are put into syringes aseptically by the Pharmacy Department at the Royal Liverpool and Broadgreen University Hospital. Albumin is added to the reconstitution based on previous similar work done by van Wassanaer et al[8]. The addition of a small amount of albumin results in a more stable solution with no decomposition products and little possibility of losses due to adsorbtion/absorption of levothyroxine into the syringe. The addition of albumin therefore allows for the availability of free thyroxine. Stability testing for the levothyroxine was performed by Quality Control North West.

Levothyroid is manufactured in Spain by Aventis Pharma, Marketing Authorisation 971622. It is imported by IDIS Ltd and prepared under EU Good Manufacturing Practice at Royal Liverpool University. Placebo will be an equal volume of 5% dextrose presented in an identical manner to the Levothyroid.

Evotrox is an oral solution and is manufactured in the United Kingdom by Kappin Ltd, Marketing Authorisation PL20249/0007. The placebo form is prepared by the Pharmaceutical company under the terms of their Marketing Authorisation as the identical carrier substance without the active ingredient. Dispensing and blinding is by the Pharmacy Departments at recruiting centres.

### Blood and Saliva Sampling

Infants: All infants will undergo blood investigations. Each sample will require approximately 0.5 ml of blood and this is arranged to coincide with routine blood tests obtained during the clinical care of the infant at the neonatal unit

TT4 (total thyroxine), FT4 (free T4), TT3 (total T3), FT3 (free T3), TSH (thyroid stimulating hormone) blood concentrations will be measured before treatment begins (baseline) and on Day 14, Day 21, Day 28 and 36 weeks (corrected age).

A subset population of infants may have more frequent blood tests for thyroid function to test the bioavailability and pharmacokinetics of the drug. The blood test will be done at different times of the day on different babies and this is arranged to coincide with routine blood tests obtained during the clinical care of the infant at the neonatal unit. Consent will be obtained separately from the parents of these infants. Since treatment allocation will be concealed, some of these infants will be receiving placebo. Comparison of drug concentrations between the two treatment groups will allow us to take account of background variation in blood thyroid concentrations.

All infants will have saliva collected from the mouth (100 microlitres) at three separate times of the day before treatment begins (baseline), on day 14, Day 28 and 36 weeks' CGA.

Early morning cortisol and ACTH concentrations will be obtained before treatment begins (baseline), on Day 14, Day 28 and 36 weeks CGA.

Mother of infant(s) enrolled: 5 ml of blood for TT4, FT4, TT3, FT3, TSH, thyroid peroxidase antibody (TPO), cortisol and thyrotropin receptor antibody (TRAB) will be obtained as soon as possible from mothers of infants who are enrolled to the study. These results will be reviewed by the study team and abnormal results will be referred to a Consultant Endocrinologist, who will liaise with the mother's Obstetrician about any follow-up that is required.

### Growth and Auxology

All infants will be measured for weight, lower leg length (using knemometry) and occipito-frontal circumference before commencing treatment (baseline), day 14, day 21, day 28 and at 36 weeks' CGA.

### Brain Imaging

Cranial ultrasounds will be performed according to the Neonatal Unit's protocol. There will be study scans at 36 weeks' CGA and routine images will be supplemented by measurements of width of the subarachnoid space.

MRI examination of the brain will be performed at term equivalence in infants for whom separate informed parental consent will be obtained, at the MRI department of the Royal Liverpool Children's Hospital, Liverpool or Wellcome Trust Clinical Research Facility, Manchester. Data acquisition is not expected to exceed 40 minutes. No sedation will be used, as infants will be imaged during natural sleep after having been fed. Careful infant positioning by the radiographer and temperature maintenance will ensure their comfort while being scanned.

### Thyroid Imaging

We will also measure thyroid gland size using ultrasound at 36 weeks' CGA. These data will be compared to published normative data for measurements of thyroid size in utero and [53]in term infants[42]. In conjunction with detailed characterisation of thyroid hormone status, this will provide a novel insight into how prematurity affects the thyroid axis.

## Summary of Investigations and Procedures

### Processing of Blood and Saliva Samples

All blood samples will be processed according to standard practice and sent to the laboratories at the Royal Liverpool Children's Hospital (Alder Hey). Saliva samples will be sent to University Department Laboratory located in the Liverpool Women's Hospital for processing (Figure 1).

**Figure 1 F1:**
[figure not shown]
Patient Flow During Trial.

### Informed Consent

The parent(s)/guardian(s) of each potentially eligible patient will be informed of the study's objectives and overall requirements after birth when the baby has achieved respiratory and haemodynamic stability. The Investigator will explain the study fully using the Patient Information Leaflet. The parent/guardian will then be given at least 12 hours to consider the study. If a parent/guardian is willing for the patient to participate in the study, he/she will be requested to give written consent. The Informed Consent Form will be signed and personally dated by both a parent/guardian and the investigator. A copy of the signed form will be provided to the parent(s)/guardian(s), another copy will be placed in they patient record, and the original retained with the research record. Nursing staff may be involved in describing the trial to the patient and his/her parent(s)/guardian(s).

A similar procedure will be followed for the elements of the study relating to MRI scans and population pharmacokinetics. An investigator will introduce the MRI scan/population pharmacokinetic study, leave the specific information leaflet and return after at least 12 hours.

### Data Management

Data will be collected on a case report form (CRF) starting at the time of recruitment. Data will be entered anonymously on to a password-protected database which will be stored in a secure office. All CRF hard copies will be duplicated and will be stored in a locked filing cabinet within the same office. Access to the database will be restricted to the investigators.

In accordance with R&D policy at LWH, the notes of all participants will be marked with a sticker to indicate study participation. A tag will be used to identify electronic records of study participants. All clinical records of study participants will be retained for 20 years. All paper and electronic records relating to the study will be retained for 20 years.

### Subject Withdrawal

Patients may be withdrawn from treatment for any of the following reasons:

a) Parent/legal representative withdraws consent.

b) Unacceptable toxicity (a potential unacceptable toxicity is defined as sustained tachycardia i.e. heart rate greater than 220 beats per minute for more than 30 minutes in a 60 minute period, in the presence of a high thyroid hormone blood concentration)

c) Intercurrent illness preventing further treatment.

d) Development of serious disease.

e) Any change in the patient's condition that justifies the discontinuation of treatment in the clinician's opinion.

If a parent/legal representative wishes to withdraw an infant from trial treatment, centres will document the reason and explain the importance of remaining on trial follow-up and, if willing, to continue to have data collected as per trial schedule, or, failing this, to attend clinic and allow routine follow-up data to be used for trial purposes. Generally, follow-up will continue unless the patient explicitly withdraws consent for follow-up. Following withdrawal from trial treatment, patients will be treated according to usual local clinical practice.

The parents/legal guardians of patients who voluntarily withdraw from the trial have previously consented to follow-up in the trial. Data up to the time of withdrawal will be included in the trial if anonymised. If the parents/legal guardians explicitly state their wish not to contribute further data to the study, the investigators will be informed and a withdrawal CRF will be completed.

## Statistical Consideration

### Sample Size Calculation

A sample size of 64 in each group will have 80% power to detect a difference between the means of the thyroxine and placebo groups of 0.67 mm (0.5*SD) for the outcome subarachnoid space at 36 weeks' CGA. This assumes that the common standard deviation is 1.3 mm and analysis is based on using a two group t-test with a 0.05 two-sided significance level. The value for the SD is taken from Armstrong et al[54] who report subarachnoid space as an indirect method of brain growth in preterm infants.

To ensure the appropriateness of the SD used in our calculations we will run an internal pilot after the first 30 infants have been randomised. We will compare the SD of these 30 infants with the standard deviation of Armstrong et al[54]. An internal pilot[49] can be used to increase but not decrease the size of the study. Assuming the 20% loss to follow up that we have experienced in an ongoing trial on the unit, we aim to recruit and randomise 150 infants with gestation below 28 weeks'.

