### Expected Serious Adverse Events

Extremely premature babies below 28 weeks' gestation constitute a high risk population: the following are serious adverse events and incidence rates which could be reasonably expected for this group of babies during the course of the study (Table 1).

**Table 1 T1:** List of Expected Serious Adverse events

Adverse event	Estimated incidence
a) death	20%*
b) necrotising enterocolitis or focal intestinal perforation diagnosed on clinical grounds, or at surgery	15%*
c) intracranial abnormality (parenchymal haemorrhage or focal white matter damage) on cranial ultrasound	15%*
d) requirement for supplementary oxygen 28 days after birth	55%*
e) patent ductus arteriosus requiring medical or surgical management	25%*
f) retinal surgery for retinopathy of prematurity	5%*
g) sustained tachycardia (greater than 220 beats per minute for more than 30 minutes in a 60 minute period)	20%**
h) pulmonary haemorrhage	5%**
i) persistent weight loss after 14 days after birth in the absence of infection.	10%**

* based on incidence of these complications at Liverpool Women's Hospital

** based on incidences estimated by the investigators

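### Randomising 150 infants with 20% loss leaves 60 per group, not the stated 64, so power at 0.5 SD is about 77.5% rather than 80%

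*Protocol article*

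**What the plan says.** All the inputs but one are in the Sample Size Calculation section of the protocol article. The requirement is "A sample size of 64 in each group will have 80% power", for a difference of "0.67 mm (0.5*SD) for the outcome subarachnoid space at 36 weeks' CGA". On variability the text says "This assumes that the common standard deviation is 1.3 mm", and the test is a "two group t-test with a 0.05 two-sided significance level". The section then allows for 20% loss to follow-up, a figure taken from experience in another trial at the unit, and concludes "we aim to recruit and randomise 150 infants with gestation below 28 weeks". It does not say whether the 20% counts deaths.

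The remaining input is Table 1 (Expected Serious Adverse Events), which lists death at 20% among "incidence rates which could be reasonably expected for this group of babies during the course of the study". The footnote gives the source of that figure as one hospital's own incidence.

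**The concern.** The number to randomise should be the number that leaves 64 evaluable infants per group once the assumed loss has occurred. It does not, and the gap is visible from figures in a single paragraph. The same sentence also gives the target difference in two forms, 0.67 mm and half an SD, which do not agree with the printed SD. A reader therefore cannot tell exactly which difference the trial is sized for.

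Attrition adds an ambiguity. The primary outcome is a scan at 36 weeks' corrected age, so an infant who dies earlier contributes nothing to it. The loss allowance and the expected mortality are both 20%, and the text does not relate them. The Subject Withdrawal section separately foresees parents refusing further data collection.

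At stake is the power attached to the primary comparison, and so how a null result is read. The Significance of the Trial section expects the trial to settle the role of the therapy.

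**Working it through.** **Inputs.** From Sample Size Calculation: 64 per group, 80% power, difference 0.67 mm or 0.5 SD, SD 1.3 mm, two-sided alpha 0.05, two-group t-test, 20% loss, 150 randomised. From Table 1: death 20%.

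**Step 1. Reproduce the 64.** Normal approximation: n = 2(1.960 + 0.842)² / d². With d = 0.5 this is 2 x 7.85 / 0.25 = 62.8, so 63. The exact two-sample t-test gives 63.8, so 64. The plan's 64 is confirmed for 0.5 SD, with power 80.2%.

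**Step 2. Inflate for loss.** N = 128 / (1 − 0.20) = 160. The plan has 150. Multiplying by 1.2 instead, a common slip, gives 153.6, so 154, which is not 150 either.

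**Step 3. What 150 delivers.** 150 x 0.80 = 120, or 60 per group. The loss that still leaves 128 is 1 − 128/150 = 14.7%.

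**Step 4. Power at 60 per group.** Noncentral t with noncentrality d√(n/2) and 118 degrees of freedom:
- d = 0.5: noncentrality 0.5 x √30 = 2.74, power 77.5% (normal approximation 78.2%).
- d = 0.67/1.3 = 0.515: power 79.95% (normal approximation 80.6%).

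**Step 5. The two forms of the effect.** 0.5 x 1.3 = 0.65 mm, not 0.67 mm. Two explanations fit:
- The SD was about 1.34 and was printed as 1.3. Then 0.5 x 1.34 = 0.67 mm, the 64 is right, and power for 0.67 mm at 60 per group is 77.5%.
- 0.67 mm and 1.3 mm are both exact. Then the normal approximation needs 60 per group, and 120/0.8 = 150 exactly. The t-test needs 60.1, so 61 per group and 122/0.8 = 152.5, so 153. On this reading 150 never belonged with 64.

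**Step 6. Sensitivity if deaths are additional to other loss.** Expected deaths are 0.20 x 150 = 30, the same number as the 30 infants allowed for. The document gives no rate of loss among survivors, so 5% to 20% is assumed here. Evaluable infants per group = 150 x 0.80 x (1 − further loss) / 2.

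| Further loss among survivors (assumed) | Per group | Power at 0.5 SD | Power at 0.67/1.3 |
|---|---|---|---|
| 0% | 60 | 77.5% | 79.95% |
| 5% | 57 | 75.4% | 77.9% |
| 10% | 54 | 73.1% | 75.6% |
| 15% | 51 | 70.6% | 73.2% |
| 20% | 48 | 67.9% | 70.5% |

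**The case against.** The definite error is small: 10 infants randomised, or 4 evaluable per group. Power falls by 2.6 points at 0.5 SD (80.15% to 77.53%), and stays within rounding of 80% if the printed millimetre figures are taken literally. The 0.67 against 0.65 discrepancy may be no more than a rounded SD. Both points stand. They limit the size of the finding but do not make 64, 20% and 150 compatible.

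The internal pilot might be thought to cover the gap, since it may increase the sample size. As described, it compares the SD in the first 30 infants with the published SD; it is not described as checking attrition.

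A reader might go further and infer that expected deaths have already consumed the whole allowance. The document does not support that, for three reasons:
- The 20% loss was observed in another trial at the unit and may already include deaths.
- Table 1's 20% is a hospital incidence, not a rate among randomised infants. Parents are approached only after the baby has stabilised, and recruitment runs to day 5, so the earliest deaths fall before randomisation.
- Table 1 covers the whole study, and some outcomes run to the expected date of delivery. A death after the 36-week scan does not remove the primary outcome.

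The two 20% figures have different denominators and time windows. That they are equal is a reason to ask for clarification. It does not prove that nothing is left for other losses.

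**Conclusion.** The sample size statement is wrong as written. On its own figures, 150 randomised with 20% loss gives 60 per group and about 77.5% power at 0.5 SD; 64 per group would need 160 randomised. This rests only on the stated loss, test and alpha. The size is modest, and it all but vanishes (79.95%) if 0.67 mm and 1.3 mm are both exact, which contradicts the 0.5 SD label.

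Whether deaths lie inside the 20% is an unresolved ambiguity in the text, not a demonstrated shortfall. The 57 to 48 per group, with about 75% to 68% power at 0.5 SD, holds only if 20% of randomised infants die before the scan and a further 5% to 20% of survivors are lost. The 48 is an assumed worst case.

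**What to change.** Rewrite the one paragraph:
- Keep 64 per group as the requirement for 80% power at 0.5 SD; that figure reproduces.
- State that 150 randomised with 20% loss yields 60 per group and about 78% power at 0.5 SD. If 80% power after 20% loss is to be kept instead, the number is 160.
- Print the SD unrounded so that 0.67 mm and 0.5 SD agree. Until that is done, do not claim 80% power for 0.67 mm at 60 per group: if 0.67 mm is half an SD, that would overstate it.
- State whether the 20% covers every reason for a missing 36-week scan, including death. If deaths are additional, add the power over an assumed range (57 to 48 per group, about 75% to 68% at 0.5 SD), labelled as sensitivity.

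Restating costs wording only and needs no extra infants; the stated power becomes slightly less favourable. The option of 160 costs 10 more infants.
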